### Intervention Group

Participants in the hydration group were coached to increase their oral water intake by 1.0 to 1.5 L/day (depending on sex and weight), over and above usual consumed beverages, for 1 year (detailed in Table 2). These water-intake levels were determined based on a review of prior literature^13,15,25,41-44^ and what we believed was safe in this population of patients with chronic kidney disease (considering that there is uncertainty in the benefit of additional water intake between 1.5 and 2.5 L/day, but risk of a total fluid intake below 1.0 L/day or greater than 4 L/day in kidney patients), and also demonstrated to be feasible in our pilot trial.^37,38^ A gradual increase in water intake was advised in the 2 weeks following randomization: during week 1, participants were instructed to consume 1 cup of water at breakfast, lunch, and dinner; and during week 2, the full amount according to weight and sex. Participants in the hydration group received reusable drinking containers and were mailed 20 vouchers per month; each voucher was redeemable for 1.5 L of bottled water.

**Table 2. table2-2054358117725106:** Hydration Intervention by Age and Sex.

Sex	Weight	Target water intake			
		Daily total (L/day)	Breakfast	Lunch	Dinner
Female	<70 kg	1.0	250 mL (1 cup)	500 mL (2 cups)	250 mL (1 cup)
	≥70 kg	1.25	250 mL (1 cup)	500 mL (2 cups)	500 mL (2 cups)
Male	<70 kg	1.25	250 mL (1 cup)	500 mL (2 cups)	500 mL (2 cups)
	≥70 kg	1.5	500 mL (2 cups)	500 mL (2 cups)	500 mL (2 cups)

### Control Group

Participants in the control group were coached to continue with their usual fluid intake or to decrease intake by 0.25 to 0.5 L/day (1-2 cups/day) if their baseline 24-hour urine volume was >1.5L/day and 24-hour urine osmolality was <500 mOsm/kg).^37^

We conducted monthly coaching with all participants (in both intervention and control groups) using interviewer-administered standardized surveys with questions on daily water intake. Coaching also included a discussion of urine color charts (showing the spectrum of dilute to concentrated urine), which were provided to all participants after randomization. Participants in the hydration group were encouraged to increase their water intake if daily intake fell below the target amount (based on sex and weight as shown in Table 2) or if they reported that their urine color was not light or clear (based on the urine color charts). Participants in the control group were asked to maintain as closely as possible the same amount ingested as reported at baseline. Coaching continued at monthly intervals for all participants for 12 months after randomization.

### Data Collection and Measures

The schedule of study measures is provided in Table 3. At baseline, a research assistant measured each participant’s height, weight, and blood pressure following a standardized protocol, and conducted an interviewer-administered health survey with questions on sociodemographics, medical history, smoking status, medication use, and fluid intake; this questionnaire also included 4 questions from the Kidney Disease Health-Related Quality of Life–Short Form (items 10, 17, 18, and 22), which relate to overall health, quality of life, and sleep.^45,46^ In addition, participants were asked about their appetite and frequency of urination during the day and night. The health survey (interviewer administered) was completed again over the phone or in person at 6 and 12 months after randomization. Weight and blood pressure were measured at the participants’ next kidney care clinic visit, approximately 8 to 12 months after enrollment. Participants also completed a 3-day diet record at baseline and again at 6 months, which they mailed back to the study center in a preaddressed postage-paid envelope; 3-day diet records were analyzed by The Food Processor (ESHA: Elizabeth Stewart Hands and Associates Research 2016 version 11.2) and a renal dietician provided individual consultations with participants to discuss their results on protein and sodium intake (participants were advised to follow a target intake of 0.8 g/kg/day of protein and 100 mmol/day of sodium).

**Table 3. table3-2054358117725106:** Schedule of Study Visits and Measures.

	Baseline^a^	Follow-up^b^					18-24 months
		3 weeks	3 months	6 months	9 months	12 months	
Survey							
Demographics	+						
Diet (3-day diet record)	+			+			
Health history	+			+		+	
Health-related quality of life	+			+		+	
Water survey	+		+	+	+		
Clinical							
Height (cm)	+						
Weight (Kg)	+				+^c^	+	
Waist circumference (cm)	+				+^c^	+	
Blood pressure (mm Hg)	+				+^c^	+	
Medications	+				+^c^	+	
Blood							
Blood sample	+	+	+	+	+	+	
Serum creatinine (μmol/L)	+	+	+	+	+	+	+^d^
Serum sodium (mmol/L)	+	+	+	+	+	+	
Urea (mmol/L)	+			+		+	
Osmolality (mOsm/kg)	+			+		+	
Copeptin (pmol/L)	+				+^c^		
Hematocrit (L/L)	+			+		+	
Cystatin C (mg/L)	+				+^c^		
HbA1c (%)	+			+		+	
Plasma samples for long-term storage	+						
Urine							
24-hour urine sample (L)	+			+		+	+^d^
Urine creatinine (mmol/d)	+			+		+	+^d^
Urine sodium (mmol/d)	+			+		+	
Urine potassium (mmol/d)	+			+		+	
Urea (mmol/d)	+			+		+	
Osmolality (mOsm/kg)	+			+		+	
Albumin (mg/d)	+			+		+	
Measured Creatinine clearance (mL/min/1.73 m^2^)	+			+		+	+^d^
Random spot urine sample	+						
Specific gravity (g)	+						
Osmolality (mOsm/kg)	+						

a Prerandomization.

b Time after randomization.

c While local labs are able to measure and process blood and urine samples, they do not measure weight, blood pressure, cystatin C, or copeptin; these measures will be obtained at the participants’ follow-up kidney care clinic visit (approximately 9 months after randomization).

d Posttrial data (18-24 months after randomization) will be obtained from participants’ medical charts where possible to reduce respondent burden. The “+” symbol indicates that the measure was collected at this time point.

Participants were instructed to collect a 24-hour urine sample (using a standard collection jug provided to them) within 2 weeks of enrollment and again at 6 and 12 months after randomization. Participants were able to deliver the 24-hour urine collection to a local laboratory (eg, LifeLabs, Gamma Dynacare, or Medical Laboratories of Windsor) or to the study center. The 24-hour urine samples were analyzed for the following measures: the albumin-to-creatinine ratio (measured using turbidimetric methods), sodium and potassium (measured using indirect potentiometry), urea (measured using enzymatic photometric methods), osmolality (measured using freezing point depression with an advanced instrument Micro-Osmometer), and creatinine clearance (body surface area corrected in mL/min/1.73 m^2^). In addition, to examine whether there was any lasting effect of the intervention after coaching stopped at 12 months, we collected data on 24-hour urine volume and creatinine from participant medical charts 18 to 24 months after randomization.

Participants provided nonfasting 10-mL blood samples at baseline, at 3 weeks after randomization, and then again at 3-month intervals after randomization until 12-months. Blood samples could be provided at the study research center or a local laboratory facility as described above. Serum creatinine was measured using the isotope dilution/mass spectroscopy–traceable enzymatic method, and eGFR was calculated using the Chronic Kidney Disease Epidemiology Collaboration (CKD-EPI) equation.^47^ Serum sodium was measured using indirect ion-selective electrodes. Other measures analyzed from blood samples at baseline and at 6 and 12 months after randomization included urea concentration (measured with enzymatic photometric methods), osmolality (measured by freezing point depression using an advanced instrument Micro-Osmometer), hematocrit (measured using Beckman Coulter automated cell counters), cystatin C (measured using immunonephelometry), glycated hemoglobin (HbA1c) (measured using nonporous ion exchange high-performance liquid chromatography), and copeptin (a glycosylated peptide that is coreleased with vasopressin from the hypothalamus^48,49^); copeptin was measured from nonfasting 150 µL blood samples, stored at −80°C, and analyzed in batches using the sandwich immunoluminometric assay (B.R.A.H.M.S. AG, Hennigsdorf/Berlin, Germany) as described by Morgenthaler et al.^48,50^ To examine whether there was any lasting effect of the intervention after coaching stopped at 12 months, we collected data on serum creatinine from participant medical charts 18 to 24 months after randomization.

### Outcomes

#### Primary outcome

The primary outcome of WIT is the change in eGFR from baseline (prerandomization) to 12 months after randomization.

#### Secondary outcomes

Key secondary outcomes include the following: Change in plasma copeptin concentration,^49,51-53^, 24-hour urine albuminuria,^54,55^ creatinine clearance, estimated 5-year risk of kidney failure (using the 4-variable Kidney Failure Risk Equation^39^), and health-related quality of life from baseline to 12 months after randomization. We will also establish the safety of increased water intake in this population by monitoring for electrolyte disturbances, particularly hyponatremia.

#### Posttrial outcomes

We will examine the between-group difference in 24-hour urine volume 18 to 24 months after randomization, and the between-group difference in eGFR change from baseline to 18 to 24 months after randomization.

### Analysis

We will use SAS version 9.3 (SAS Institute Inc, Cary, NC) for all statistical analysis.

The primary analysis will follow an intention-to-treat approach. The between-group difference on change in eGFR (calculated as eGFR at 12 months minus eGFR at baseline) will be analyzed using linear regression. The following prespecified covariates (measured at baseline) will be adjusted for in the primary analysis: age (in years), sex, obesity (body mass index ≥30 kg/m^2^), smoking status (current smoker: yes/no), presence of diabetes, albuminuria (mg/d), and use of any of the following medications: an angiotensin-converting enzyme inhibitor or angiotensin receptor blocker, diuretics, beta blockers or calcium channel blockers, and statins. We will include a missing data indicator value for each covariate.^56^ We expect that 12-month data on eGFR will be missing for <5% of participants due to death and <10% due to missing data or study withdrawal. For patients who were randomized but are missing a 12-month eGFR value, we will use recommended model-based multiple imputation methods to impute the final eGFR value.^57-59^ We will perform sensitivity analyses, including a complete-case analysis, to investigate whether conclusions are sensitive to assumptions about the missing-data mechanism.^57-59^

We will report the primary outcome as the absolute difference in 12-month eGFR change between randomized groups with a 95% confidence interval. Our current sample size of 631 randomized participants will provide 80% power to detect a difference of at least 1.8 mL/min/1.73 m^2^ between intervention groups (α = 0.05, independent samples *t* test, assuming a standard deviation of 8), which represents a small-to-moderate effect size. The primary analysis will be performed 12 months after the last patient has been randomized (date of final follow up expected in June 2017).

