### Secondary Outcomes

Changes in continuous secondary outcomes (plasma copeptin concentration, creatinine clearance, the 24-hour urine albuminuria, and the 5-year Kidney Failure Risk Equation developed by Tangri et al^39^) will be analyzed using linear regression as described above. Variables will first be assessed for normality and, if not normally distributed, will be transformed as appropriate. Finally, we will also examine the relationship between change in copeptin and kidney function, and examine whether this relationship differs between intervention groups. For all secondary analyses, including health-related quality of life, all between-group differences will be reported using 95% confidence intervals.

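### The primary regression of eGFR change does not adjust for baseline eGFR; adding it would improve precision and handling of chance imbalance at almost no cost

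*Protocol article*

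**What the plan says.** The Analysis section defines the outcome and the model together: "The between-group difference on change in eGFR (calculated as eGFR at 12 months minus eGFR at baseline) will be analyzed using linear regression". It then names the adjustment set. "The following prespecified covariates (measured at baseline) will be adjusted for in the primary analysis: age (in years), sex, obesity" opens the list, which continues with "smoking status (current smoker: yes/no), presence of diabetes, albuminuria (mg/d), and use of any of the following medications", the medications being "an angiotensin-converting enzyme inhibitor or angiotensin receptor blocker, diuretics, beta blockers or calcium channel blockers, and statins". Counting each medication group once gives ten covariates. Baseline eGFR is not among them, and nothing elsewhere in the article adds it to this model; the abstract says only that linear regression will be used. Baseline eGFR therefore enters only by subtraction.

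The Randomized Allocation section stratifies by center and gender, so baseline eGFR is not balanced by design. The Secondary Outcomes section carries the same model over to copeptin, creatinine clearance, albuminuria and the kidney failure risk score, whose changes "will be analyzed using linear regression as described above".

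**The concern.** Subtracting a baseline is not the same as adjusting for it. A change score without its baseline in the model fixes the slope of follow-up on baseline at exactly 1. Creatinine-based eGFR is a noisy repeated measure, and noise in the baseline value pulls that slope below 1. Two things then follow. Part of the residual variance could have been explained and is not. And if the arms differ by chance at baseline, subtraction over-corrects: the arm that starts higher is credited with too little.

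This affects the single primary estimate. It also reaches the three supporting eGFR analyses, because their significance is read only in concordance with the primary result. Recruitment is closed, so precision can no longer be gained by enrolling more patients, whereas baseline eGFR is already scheduled for every participant.

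**Working it through.** **Inputs from the article (Analysis section).** N = 631, 80% power, difference 1.8 ("Our current sample size of 631 randomized participants will provide 80% power to detect a difference of at least 1.8"), α = 0.05, and "assuming a standard deviation of 8". I read 8 as the SD of the 12-month change and the test as two-sided; the article states neither.

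**Inputs that are assumptions.** The article gives no baseline SD and no slope b of 12-month on baseline eGFR. Eligibility is eGFR 30 to 60; a uniform spread over that window has SD 30/√12 = 8.66. I vary b from 1.0 down to 0.6.

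**Step 1: the plan's own figure.** With 1:1 allocation, SE = 8 × √(4/631) = 0.637. Power = Φ(1.8/0.637 − 1.96) = 80.7% (80.6% with the exact t distribution). The detectable difference at 80% power is 2.8016 × 0.637 = 1.78. The stated figure reproduces.

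**Step 2: precision with baseline eGFR in the model.** Regressing the change on baseline eGFR gives a slope of b − 1, so

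residual variance = 64 − 8.66² × (1 − b)², with 8.66² = 75.

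For example, at b = 0.8 this is 64 − 75 × 0.04 = 61, residual SD 7.81.

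**Step 3: effect of chance imbalance.** If the arms differ at baseline by D, the expected change-score estimate given D is (true effect) + bD − D = (true effect) − (1 − b)D. The 95% limit of D is 1.96 × 8.66 × √(4/631) = 1.35.

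| b | Residual SD | Variance reduction | Power for 1.8 | Detectable difference | Shift at D = 1.35 |
|---|---|---|---|---|---|
| 1.0 | 8.00 | 0% | 80.7% | 1.78 | 0 |
| 0.9 | 7.95 | 1.2% | 81.1% | 1.77 | 0.14 |
| 0.8 | 7.81 | 4.7% | 82.5% | 1.74 | 0.27 |
| 0.7 | 7.57 | 10.5% | 84.8% | 1.69 | 0.41 |
| 0.6 | 7.21 | 18.7% | 88.0% | 1.61 | 0.54 |

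The shift has the opposite sign to D.

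**Step 4: sensitivity to the baseline SD.** For b = 0.9, 0.8 and 0.7, a baseline SD of 7 gives power of 81.0%, 81.9% and 83.4%, with shifts of 0.11, 0.22 and 0.33. A baseline SD of 10 gives 81.3%, 83.1% and 86.2%, with shifts of 0.16, 0.31 and 0.47.

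**Step 5: simulation.** With 4,000 runs per slope, a uniform 30-60 baseline and a true effect of 1.8, both estimators centred on 1.8. Their standard errors were 0.641 (change score) and 0.625 (adjusted) at b = 0.8, and 0.640 and 0.609 at b = 0.7.

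**The case against.** The strongest reply is that nothing here is wrong. Under 1:1 randomization the change-score regression is unbiased on average and keeps its type I error, and the power statement, made for an unadjusted t test, is correct. That stands in full. A reader might infer that the primary estimate is biased or the trial underpowered by this omission; the documents do not support either. The shift in Step 3 is conditional on the allocation that happens to be realised. It vanishes at b = 1, and the values in the table need an imbalance at the edge of its 95% range.

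The second reply concerns size, and it also stands. A reader might assume equal SDs at both visits and arrive at much larger gains: baseline and 12-month SDs of 8 imply a slope of 0.50, a residual SD of 6.93 and power of about 90%. No document supports that slope. Equal SDs are also doubtful when entry restricts the baseline to 30-60 and nothing restricts the 12-month value; with SDs of 9 and 12 the gain is nil. A baseline SD of 10 is hard to reach inside that window. Nor does the window itself argue for a slope below 1, since selecting on baseline does not change the linear slope of follow-up on baseline; only measurement noise does. Finally, the listed covariates, age and albuminuria among them, may already absorb part of the association, so the gain over the planned model may be smaller than the table shows.

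Two extensions should not be drawn. The omission does not affect every secondary outcome, because baseline albuminuria is on the list and serves the albuminuria model. And the article names no predictors for the multiple imputation, so nothing shows that baseline eGFR is left out there.

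It could also be said that an article condenses and the analysis plan may add the covariate. If it does, the point falls away; but the article does not leave the adjustment set open. It names the set and calls it prespecified.

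**Conclusion.** The omission is certain on the text; its size is not. The planned analysis is valid, and this is a nearly free improvement in precision and in conditional bias rather than an error. Under a baseline SD of 8.66 and slopes of 0.9 to 0.7, adjustment is worth roughly half a point to four points of power, and it removes a shift of 0.14 to 0.41 mL/min/1.73 m² at the 95% limit of imbalance, that is 8% to 23% of the 1.8 target (0.14/1.8 and 0.41/1.8). The gain is zero at b = 1 and larger at lower slopes. These figures rest on reading 8 as the SD of change, on the assumed baseline SD and slopes, and on comparison with an unadjusted analysis.

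**What to change.** Before unmasking, add continuous baseline eGFR to the covariates of the primary regression. The quantity estimated, the difference in mean 12-month change, stays the same; with baseline in the model, analysing change or the 12-month value gives the same treatment effect. In the same amendment, add baseline copeptin, baseline creatinine clearance and the baseline kidney failure risk score each to its own model, on the same scale as the outcome if that is transformed. Albuminuria needs no addition. Keep the regression with the ten listed covariates as a sensitivity analysis.

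The cost is one degree of freedom per model and a dated amendment, with no new data collection. Timing matters: the statistician is to be blinded to allocation for the primary analysis, so the change is credible now and would look data-driven once allocation is known.

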## Methods

### Design, Setting, and Participants

WIT is a parallel-group, open-label, 9-center randomized controlled trial. Recruitment and randomization (detailed below) occurred between May 2013 and May 2016; follow-up for the primary outcome will continue until June 2017 (trial registration: www.clinicaltrials.gov; government identifier: NCT01766687). Ethics approval was obtained from Western University’s Health Sciences Research Ethics Board.

Adult patients with stage 3 chronic kidney disease were recruited from 9 chronic kidney disease clinics across Southwestern Ontario (Canada) in London (3 centers), Guelph (1 center), Hamilton (1 center), Oakville (2 centers), and Windsor (2 centers). The patient’s nephrologist invited interested potential participants to speak with a research assistant who explained the study and confirmed study eligibility (patient eligibility criteria are fully detailed in Table 1). All participants had to have stage 3 chronic kidney disease (eGFR 30-60 mL/min/1.73 m^2^) and microalbuminuria (defined as albumin/creatinine >2.8 mg/mmol if female, or >2.0 mg/mmol if male, or trace protein or greater from a random spot urine sample on an Albustix).^40^ Exclusion criteria (fully detailed in Table 1) included self-reported fluid intake ≥10 cups/day or a 24-hour urine volume ≥3L; a history of kidney stones in the past 5 years; or currently taking lithium, hydrochlorothiazide >25 mg/day, indapamide >2.5 mg/day, furosemide >40 mg/day, or metolazone >2.5 mg/day.

**Table 1. table1-2054358117725106:** Eligibility Criteria for the Chronic Kidney Disease Water Intake Trial.

Inclusion criteria
● Age between 18 and 80 years. ● Able to provide informed consent and willing to complete follow-up visits. ● Estimated glomerular filtration rate between 30 and 60 mL/min/1.73 m^2^. ● Trace protein or greater (Albustix) or urine albumin/creatinine ratio ≥2.8 mg/mmol (if female) or ≥2.0 mg/mmol (if male) from a random spot urine sample. ● Ability to read and speak English.
Exclusion criteria

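### Minor efficiency point: the primary model cuts BMI at 30 and, on its natural reading, enters baseline albuminuria as a raw linear term in mg/d

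*Protocol article*

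**What the plan says.** The Analysis section states that the difference between groups in 12-month eGFR change "will be analyzed using linear regression", adjusted for a prespecified list of baseline covariates. Age is listed by its unit (years). Smoking is a yes/no item. Body size enters as "obesity (body mass index ≥30" kg/m². Albuminuria appears within "presence of diabetes, albuminuria (mg/d), and use of any of the following medications", again by unit only.

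Table 1 admits patients with "Trace protein or greater (Albustix) or urine albumin/creatinine ratio" at or above a sex-specific threshold: "urine albumin/creatinine ratio ≥2.8 mg/mmol (if female) or ≥2.0 mg/mmol (if male) from a random spot urine sample". No upper limit on albuminuria is given among the eligibility criteria.

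The Secondary Outcomes analysis section, which covers 24-hour albuminuria as an outcome, says: "Variables will first be assessed for normality and, if not normally distributed, will be transformed as appropriate". The Analysis section has no such sentence for the primary model. The continuous secondary outcomes use the same regression approach.

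**The concern.** Adjustment in a randomised trial is done mainly for precision, and the gain depends on how well each covariate's form matches its relation to the outcome. A variable with a floor and no ceiling is likely to be right-skewed. The plan allows for skew when albuminuria is an outcome but not when it is a covariate in the primary model. Entered raw, the term is driven largely by its upper tail and may pick up only part of the outcome variation that albuminuria explains. Cutting BMI at 30 likewise discards information, although height and weight are both measured at baseline. At stake is a modest amount of precision that could be had from data already collected.

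**Working it through.** **Plan's own figure.** Inputs from the Analysis section: 631 participants, difference 1.8 mL/min/1.73 m², SD 8, α = 0.05 (two-sided). Allocation is 1:1.
- SE = 8 × √(4/631) = 0.637.
- Power = Φ(1.8/0.637 − 1.96) = Φ(0.87) ≈ 80.7%, which reproduces the stated 80%.
- Detectable difference at 80% power = 0.637 × (1.96 + 0.84) = 1.78.

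This is an unadjusted t test, so it takes no credit for any covariate.

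**Assumptions, not in the article.** Albuminuria is log-normal with log-SD 1.0 or 1.5. eGFR change is linear in log albuminuria, with R² from 0.01 to 0.10.

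**How much a raw term keeps.** Let r² be the squared correlation between log and raw albuminuria. Its simulated mean at n = 631 is 0.609 (log-SD 1.0) and 0.363 (log-SD 1.5). The raw term then explains R² × r² of the outcome variance. Under the same assumption, the top 32 patients (about 5%) hold about 72% and 88% of the raw covariate's sum of squares.

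**Effect on the treatment estimate.** Variance ratio, log to raw = (1 − R²)/(1 − R² × r²). Power uses a residual SD of 8√(1 − R²) for log and 8√(1 − R² × r²) for raw. Equivalent patients = 631 × (1/ratio − 1).

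| log-SD | R² | Variance ratio | Power raw → log | Gain (points) | Equivalent patients |
|---|---|---|---|---|---|
| 1.0 | 0.01 | 0.996 | 80.9 → 81.1% | 0.2 | 2 |
| 1.0 | 0.03 | 0.988 | 81.4 → 81.8% | 0.5 | 8 |
| 1.0 | 0.05 | 0.980 | 81.9 → 82.6% | 0.8 | 13 |
| 1.0 | 0.10 | 0.958 | 83.0 → 84.6% | 1.5 | 27 |
| 1.5 | 0.01 | 0.994 | 80.8 → 81.1% | 0.2 | 4 |
| 1.5 | 0.03 | 0.981 | 81.1 → 81.8% | 0.7 | 12 |
| 1.5 | 0.05 | 0.968 | 81.4 → 82.6% | 1.2 | 21 |
| 1.5 | 0.10 | 0.934 | 82.1 → 84.6% | 2.5 | 45 |

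Gains are from unrounded powers. Worked example for the last row: 0.90/(1 − 0.10 × 0.363) = 0.90/0.9637 = 0.934.

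On the outcome scale, the unadjusted 95% CI half-width is 1.96 × 0.637 = 1.25. In the last row it goes from 1.25 × √0.9637 = 1.23 (raw) to 1.25 × √0.90 = 1.19 (log), about 0.04 mL/min/1.73 m² narrower.

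**Validity.** 4,000 simulated null trials were run with a true log relation (R² 0.10) but a raw linear term. At log-SD 1.5, type I error was 0.054 and mean bias −0.01. At log-SD 2.0 they were 0.045 and 0.00. The Monte Carlo SE of the error rate is √(0.05 × 0.95/4000) = 0.003, so both rates are compatible with 0.05.

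**BMI.** A cut near the median of a normal variable keeps 2/π ≈ 64% of its R². For an assumed R² of 0.01 to 0.03, continuous BMI adds 0.1 to 0.4 power points.

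**The case against.** **The form is inferred.** The article gives a unit, not a functional form, and a covariate's form is often left to an analysis plan that is not shown here. This stands in part: a raw term is a reading, not a statement. But the list is closed and prespecified, it says so where a category is meant, and it treats albuminuria exactly as it treats age. The BMI cut is explicit on any reading.

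**The size is built in.** The calculation assumes the log model is right. Squared correlation is symmetric, so if eGFR change were linear in mg/d, the log term would capture only 61% or 36% of what the raw term explains, and the proposed change would lose precision by the same formula. This stands. The log form is a judgement about a variable likely to be skewed, and these documents cannot prove it.

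**The effect is negligible.** Stated power does not depend on albuminuria, and the gain is at most a few points. This stands as to size and makes the point minor.

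**The secondary models may already be covered.** The transformation rule speaks of variables, so it could be read to include covariates there. That is possible, and it is a reason to settle one list for all models.

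A reader might also infer that a few patients with very heavy albuminuria dominate the model, or that chance imbalance among them threatens the treatment estimate. The documents support neither. They give no albuminuria distribution, so the shares of the sum of squares above belong to the assumed log-normal. Randomisation protects the estimate, and the simulation shows negligible bias and near-nominal type I error.

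**Conclusion.** The point holds as a minor matter of efficiency. On its natural reading the primary covariate list uses a raw scale for a variable likely to be skewed, and it explicitly dichotomises BMI. The log form is worth a variance reduction of about 0.4% to 7% and 0.2 to 2.5 power points, given log-normal albuminuria (log-SD 1.0 to 1.5) and eGFR change linear in log albuminuria with R² 0.01 to 0.10. More extreme assumptions (log-SD 2.0, R² 0.15) give 4.6 points. Continuous BMI adds a few tenths of a point. Nothing here makes the stated 80% power wrong or the planned analysis invalid. It would also be too strong to say that a raw term removes little of what albuminuria explains: at log-SD 1.0 it still keeps 61%.

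**What to change.** Before unblinding, change two entries in the primary covariate list:
- enter baseline albuminuria as its natural logarithm, with values below the assay limit set to that limit so that the log is defined;
- enter BMI as a continuous term in place of the obesity indicator.

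State that the same list applies to the secondary outcome models. If a log term was always intended, the same line removes the ambiguity.

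The cost is one line in the analysis plan. Urine albumin, height and weight are already collected at baseline, and the trial statistician is to be blinded for the primary analysis. There are two downsides: the albuminuria coefficient is read on a log scale, and a little precision would be lost if the true relation were linear in mg/d.

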### Randomized Allocation

Once study eligibility was confirmed, a research assistant contacted the participant by telephone to complete the randomization; concealed randomized allocation occurred by computer-generated randomization while the participant was on the phone. Participants were randomized (1:1) in random permuted blocks of varying sizes to the hydration group or the control group, stratified by center and gender. By necessity, research staff and participants were aware of the randomized group assignment; however, outcome assessors (technicians performing the laboratory measurements for the primary and secondary outcomes) are blinded to the random allocation, and the trial statistician will be blinded to patient allocation for the primary analysis.

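### The stated 80% power for 1.8 mL/min/1.73 m² needs a 12-month eGFR from nearly all 631 participants, while the same section expects some missing; unadjusted power falls to about 74% at the 15% ceiling

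*Protocol article*

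**What the plan says.** All of this stands in the Analysis section of the protocol article, apart from the allocation ratio.

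- Power: "Our current sample size of 631 randomized participants will provide 80% power to detect a difference of at least 1.8 mL/min/1.73" m². The basis is given as "α = 0.05, independent samples *t* test", "assuming a standard deviation of 8".
- Allocation (Randomized Allocation section): "Participants were randomized (1:1) in random permuted blocks of varying sizes".
- Expected loss, in the paragraph just before the power sentence: 12-month eGFR is expected to be "missing for <5% of participants due to death and <10% due to missing data or study withdrawal".
- Handling of loss: a missing 12-month eGFR is multiply imputed in the primary analysis, and a complete-case analysis is among the sensitivity analyses.
- Primary model: linear regression on the change in eGFR, adjusted for a listed set of baseline covariates. The power sentence does not use this adjustment.

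**The concern.** The power sentence counts participants randomised. The precision of the primary comparison depends on how many have a 12-month eGFR, or on how well the missing values can be predicted. The section gives its own expectation of loss and then states power as if there were none.

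Recruitment was complete when the article was written, so the sentence describes what a fixed sample can detect. If it makes no allowance for the loss that the authors themselves expect, readers are told that the trial is somewhat more sensitive than its stated inputs support.

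**Working it through.** **Inputs.** N = 631, difference δ = 1.8, SD σ = 8, α = 0.05 and a two-sample t test (Analysis section); 1:1 allocation (Randomized Allocation section). The article does not say whether α is one- or two-sided. Two-sided is taken because it reproduces the stated 80%; one-sided α would give about 88%.

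**Formula.** With N observed outcomes split equally, the standard error of the difference is SE = σ·√(4/N) and the noncentrality is δ/SE. Power comes from the noncentral t distribution with N − 2 degrees of freedom. The detectable difference is the δ that gives 80% power.

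**Step 1: reproduce the stated figure.** With N = 631, SE = 8·√(4/631) = 0.637 and 1.8/0.637 = 2.826. Power is 80.6%. The difference detectable with 80% power is 1.787, which rounds to the stated 1.8. The calculation is right for complete outcomes.

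**Step 2: how much loss does it tolerate?** 80% power for 1.8 needs about 622 observed outcomes. (631 − 622)/631 = 1.4%, so the stated power survives a loss of only about 1%.

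**Step 3: apply the expected loss.** The two ceilings sum to 5% + 10% = 15%. Observed N = 631 × (1 − proportion missing).

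| Missing | Observed N | SE | Power for 1.8 | Detectable with 80% power |
|---|---|---|---|---|
| 0% | 631 | 0.637 | 80.6% | 1.79 |
| 5% | 599 | 0.654 | 78.5% | 1.83 |
| 10% | 568 | 0.671 | 76.3% | 1.88 |
| 15% | 536 | 0.691 | 73.9% | 1.94 |

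At the ceiling the change is 80.6 − 73.9 = 6.7 percentage points of power, and 1.94 − 1.79 = 0.15 mL/min/1.73 m² in the detectable difference.

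**Step 4: what could offset it.** The article gives no correlation and no R², so the values here are assumptions, all taken at 15% missing (536 observed, 95 missing).

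- *Imputation from earlier eGFR.* Let ρ be the correlation between the missing value and its prediction. The effective N is then roughly 536 + 95ρ². For ρ = 0.5, 0.7 and 0.8 this is about 560, 583 and 597, with power 75.7%, 77.4% and 78.3%.
- *Covariate adjustment.* If the covariates explain a share R² of the variance, σ becomes 8·√(1 − R²). With 536 observed, R² = 5% gives 76.0%, 10% gives 78.2% and 14% gives 80.1%.
- *Both together.* With ρ = 0.7, R² = 5% gives 79.4% and R² = 10% gives 81.5%.

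**The case against.** The strongest reply has four parts.

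**The calculation is not wrong.** From 631, SD 8 and α = 0.05 the stated power follows. This stands. A reader might infer a computing error; there is none. The fault is that the figure sits beside an expectation of loss that it does not reflect.

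**15% is a ceiling, not the plan.** Both rates are given as less-than bounds. This stands too. A reader might conclude that the trial is designed for 15% missing and therefore has 74% power. The article does not say so. The range from 5% to 15% is the fair statement, and 73.9% is its lower end.

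**Imputation and adjustment recover information.** A reader might hold that multiple imputation can restore nothing. That goes too far. Serum creatinine is scheduled at 3 weeks and at 3, 6 and 9 months (Table 3), and an imputation model that uses these values would recover part of the loss. Patients lost early would gain less. Covariate adjustment may also reduce the residual variance, and the two together could bring power back to 80%. But the article does not say whether the earlier values enter the imputation, states no R², and bases its power on an unadjusted t test. A gain that is possible but not claimed does not support the printed figure. Equally, its absence is not shown, so one cannot say that the primary analysis will have less than 80% power.

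**Little depends on it.** The result is to be reported with a 95% confidence interval, which will show the precision actually achieved and is the better guide to a null result. Enrolment is closed, and an SD of 7.4 instead of 8 would by itself give 80% with 536 observed. This limits the importance of the point. It does not make the sentence consistent with the paragraph before it.

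**Conclusion.** The point holds as a mismatch between two statements in one section. On its own stated basis, the 80% power for 1.8 mL/min/1.73 m² requires a 12-month eGFR from about 622 of 631 participants. With 5% to 15% missing, unadjusted power is 78.5% down to 73.9%, and the difference detectable with 80% power is 1.83 to 1.94.

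This rests on two-sided α, equal groups, SD 8 and no gain from imputation or covariates. Some gain is plausible and could close the gap, but its size cannot be derived from the article. The effect is modest, and neither the primary analysis nor the validity of the trial is in question. The documents do not support a reading that the trial is seriously underpowered or should have enrolled more.

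**What to change.** Restate the power sentence for the number expected to have an outcome, and name its basis. For example:

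*With 631 randomised and up to 15% without a 12-month eGFR (about 536 observed), the trial has 80% power for a difference of about 1.9 mL/min/1.73 m² (at least about 74% for 1.8), assuming SD 8 and an unadjusted two-sided t test at α = 0.05, before any gain from imputation or covariate adjustment.*

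Alternatively, keep 1.8 with 80% power and state the gain from imputation or covariate adjustment that it relies on, with the assumed correlation or R².

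The cost is one sentence and a slightly less favourable figure. No enrolment, data collection or analysis changes.
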